## Abstract

Age-related changes increase frailty and vulnerability to stress in older adults, and stress has been linked to poorer balance and fall risk. However, the mechanisms by which emotional stress may contribute to falls remain unclear. This study explores whether: 1) emotional stressors lead to neuromuscular changes that affect postural control in older adults; and 2) technology can assist in fall prevention by detecting increased risk. A cross-sectional, laboratory-based observational study is being conducted in a single session comparing 30 young adults (18–39 years) and 30 older adults (≥65 years), in which participants are exposed to emotional stressors (high-arousal images) and their immediate neuromuscular and balance responses are recorded. The first participant was enrolled on November 27, 2024. All participants complete a sequence of physical tasks under two conditions: viewing low-arousal and high-arousal images from the International Affective Picture System. The physical tasks involve standing up from a chair, walking to a table, transferring water between bottles, returning to the chair, and sitting down. Emotional responses are assessed using heart rate variability, respiratory rate and subjective feelings of unease. Electromyographic signals are analysed using wearable sensors, ground pressure is recorded via pressure sensors and bottle manipulation is tracked with inertial measurement units. Furthermore, balance is evaluated using the Timed Up and Go Test and the Functional Reach Test, administered before the low-arousal condition and after the high-arousal condition. Comprehensive data analysis will provide new insights to aid professionals in designing interventions for detecting and preventing fall risk in older adults. The study was approved by the corresponding ethics committee and registered at ClinicalTrials.gov (NCT06682754) on November 21, 2024. It is being conducted at the University of Alcalá, Spain, and is funded by the European Union and the ‘Junta de Castilla-La Mancha’. Principal investigators are [name] and [name] ([contact]). The collected data will be anonymized and shared in an open-access repository, in line with ethical and open science principles.

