### Participants

Participants are divided into two groups: young adults (18–39 years) and older adults (≥65 years). Inclusion criteria are: age between 18–39 years for the young group or ≥65 years for the older group; ability to understand spoken and written Spanish sufficiently to follow the study information and instructions; corrected or uncorrected vision sufficient to view the image-based tasks; ability to walk safely over short distances in the laboratory setting, with or without usual assistive devices; and willingness to provide written informed consent. Participants are included if they wish to take part voluntarily and do not present any of the following exclusion criteria: illness, injury or previous trauma that contraindicates muscle exertion, balance exercises and/or walking; physical or mental illness that contraindicates exposure to emotionally stressful stimuli, such as severe depression or psychosis; or difficulty understanding the study information and signing the consent form.

To calculate the sample size, an a priori power analysis was performed. The significance level (α) was set at 0.05, with a statistical power (1 – β) of 0.80, assuming a medium effect size (f = 0.25) to detect the main interaction effect between the group factor (younger vs. older adults), and the stimulus factor (non-stressful vs. stressful) in the context of a 2x2 Mixed ANOVA (F-test, two tails). The selection of a medium effect size is justified because the induction of emotional stress causes a robust and quantifiable functional disruption in older adults’ balance reactions, which has been demonstrated in previous studies [12]. G*Power version 3.1.9.7 was used, and it was determined that the required sample size was 27 participants per group. Assuming a potential dropout rate of 10%, the minimum initial sample size is 30 participants for each group.

Young participants are recruited from various schools at the University of Alcalá (UAH), the Complutense University of Madrid (UCM) and other settings such as sports clubs or student associations. Older participants are recruited through contacts at the University for Older Adults at UAH, the Alcalá City Council, associations, residential centres and others.

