#### Baseline physical assessment.

Physical assessment provides insight into the physical condition of the participants.

Frailty is assessed using the Short Physical Performance Battery (SPPB) whose validity, reliability and reference values have been established in older spanish adults [26]. The SPPB consists of three components that assess balance, gait speed and the ability to stand up from and sit down on a chair five times. Each component is scored out of 4 points, based on the time taken by the participant to complete each task. A total score of less than 10 is considered indicative of a high likelihood of frailty [27].

Balance is evaluated using the Spanish version of the Mini Balance Evaluation Systems Test (Mini-BESTest), which has shown good psychometric properties in community-dwelling older adults [28]. This test includes 14 items that assess anticipatory postural adjustments, postural responses, sensory orientation and dynamic gait stability. Each item is rated on a scale from 0 to 2. Lower scores indicate greater balance impairment [28]. Additionally, the Mini-BESTest includes the Timed Up and Go Test (TUG), conducted both with and without a dual task. The TUG [29] measures the time it takes for the participant to rise from a chair, walk three metres, turn around, return to the chair and sit down again. Three trials are conducted, and times exceeding 12 seconds are interpreted as indicative of high frailty risk [27]. In the dual-task TUG, participants are also asked to count backwards in threes from a specified number before and during the task. A reduction in walking speed of more than 10% between the single and dual-task TUG, or stopping either the walking or the counting, indicates increased frailty. Balance is also assessed using the Functional Reach Test (FRT), for which a Spanish version has demonstrated good validity and reproducibility in older adults [30]. This test measures how far a person can reach forward while maintaining their balance without moving their base of support. Greater reach distances indicate a lower risk of falls.

All these tests are performed at the beginning of the study. In addition, the TUG and FRT are repeated after the intervention (Fig 2).

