#### Outcome measurements.

The primary outcome measures are:

Changes in muscle activity [31], monitored through surface electromyography (EMG). EMG signals are recorded using Delsys Trigno system devices (Delsys Inc., Boston, USA), offline mode, 1259 Hz sampling bilaterally on the biceps brachii, multifidus, gluteus medius, biceps femoris, medial gastrocnemius, vastus lateralis and tibialis anterior. Electrodes are placed following SENIAM guidelines [32]. After placement and prior to the experimental session, two maximum voluntary contractions (MVCs) are performed for each muscle, with a six-second rest in between. These MVCs are used for data normalisation in subsequent analyses. Time-based EMG outcome measures include the root mean square (RMS), synchronisation of activation between muscle groups, and the ratio of activation between muscles. Frequency-based measures include the median frequency (MDF). EMG data are collected only during motor task testing, both at baseline (t_1_) and during the experimental test (t_2_) for all participants. No EMG recording occurs during baseline physical assessments (SPPB, Mini-BESTest/TUG, FRT), which characterize participant frailty prior to stress exposure (Fig 2).Ground pressure is measured using a custom-made Fitness MAT DEV KIT 1.9 mat (80 × 80 cm) developed for this project (Sensing Tex S.L., Sant Cugat del Vallès, Spain). This mat includes pressure sensors that provide precise information on weight distribution and participant behaviour during weight-shifting tasks [33]. The mat features a sensing area of 160 × 56 cm and a matrix of 2,240 sensors with a spatial resolution of 20 mm between sensors (80 × 28 matrix), local pressure mapping. Each pressure sensor has a measurement range of 20–10,000 mmHg, with 10% accuracy and a linearity coefficient of 0.99. Data are collected using a 12-bit resolution electronic unit with Bluetooth and USB connectivity. Pressure data are recorded during motor task tests at both baseline (t_1_) and the experimental test (t_2_).Acceleration and deceleration during object manipulation are measured using WT9011DCL devices (WitMotion ShenZhen Co. Ltd., ShenZhen, China). These triaxial IMUs are attached to the bottles participants must handle during fine motor task tests. Data are recorded during both baseline (t_1_) and experimental (t_2_) sessions for all participants.Balance, additionally assessed using the TUG and FRT before and after the experimental session.

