#### Intervention.

Images from the International Affective Picture System (IAPS) [34] are used during both the baseline (t_1_) and experimental (t_2_) sessions to expose participants to non-stressful and emotionally stressful stimuli, respectively. The IAPS is one of the most widely used standardised image sets for inducing emotions in experimental research. It has been shown to reliably elicit measurable changes across the three emotional response systems: subjective-verbal, behavioural and physiological [35]. For the baseline (t_1_), 40 low-arousal IAPS images have been selected, which collectively produce a mean arousal rating below 2.4 in both young and older adults, based on normative data from previous studies [36]. For the experimental session (t_2_), 40 high-arousal IAPS images were selected, collectively producing a mean arousal rating above 6.7 in both young and older adults [36].

Potential risks: no physical risks from assessments (supervised by trained professionals). High-arousal IAPS images may cause transient emotional discomfort, resolving shortly after exposure (“the sensation will pass shortly” -participant information sheet). Data security breach risk minimized through pseudonymization (unique codes from outset), local storage (UAH servers/OneDrive private folder, researcher access only; physical data under lock/key), and GDPR compliance (EU 2016/679, LOPDGDD 3/2018) – no identifiable personal data collected).

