### Procedure

All study procedures are completed in a single laboratory visit. The study is conducted in the laboratories of the University of Alcalá (UAH), located in the Polytechnic Building and the Nursing and Physiotherapy Building. The researcher first provides verbal explanation of the study, answers all questions, and gives participants the information sheet (attached as Supplementary Information S1 File) to read, take home, and discuss with others as needed. Participants confirm understanding and sign the Informed Consent form only when ready. Firstly, participants read the information sheet and sign the Informed Consent form. Following this, baseline cognitive and physical assessments are carried out (Fig 2).

During the baseline test (t_1_) and the experimental test (t_2_), all participants perform the same tasks and wear both the Delsys Trigno system devices and the Hexoskin vest.

The baseline test (t_1_) is conducted first. Fixed order (low- then high-arousal) mimics real-life stress exposure patterns for ecological validity and avoids carryover effects from randomization. Participants are asked to sit on a stable chair and view low-arousal IAPS images for three minutes. After this period, a signal is given for them to begin the motor task test (gross motor, fine motor and balance tasks). This motor task test involves standing up from the chair, walking 2.3 metres over the pressure mat to a table, emptying the contents of one bottle (water) into another positioned on the table, turning around, walking back to the chair and sitting down again (Fig 3). Low-arousal IAPS images continue to be projected during the motor task test (Fig 2).

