**Fig 3 pone.0341744.g003:**
[figure not shown]
Diagram of the area for carrying out motor tasks. By the authors.

Next, the experimental test (t_2_) is performed. With participants once again seated, they are asked to view high-arousal IAPS images for three minutes. After three minutes, they receive a signal to repeat the same motor task test (gross motor, fine motor and balance tasks) as in the baseline test (t_1_). During the execution of these motor tasks, high-arousal IAPS images continue to be projected (Fig 2).

Afterwards, the TUG and FRT are repeated. Finally, the Delsys Trigno system devices and the Hexoskin vest are removed.

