To assess whether the emotionally stressful stimulus produces psychophysiological effects in participants, secondary outcome variables will first be assessed: HRV, RR, and VAS of unease. Once the effect of stress has been verified, changes in the primary outcome variables will be evaluated: muscle activity (RMS y MDF), ground pressure, acceleration and deceleration, TUG, and FRT. All analyses will be conducted using mixed factorial ANOVAs, assessing the between-subjects factor GROUP (young, older adults) and the within-subjects factor TIMEPOINT (baseline, experimental). Type I error will be set at α = 5%, and partial eta squared (*η*_*p*_*²*) will be calculated as a measure of effect size. To control for multiplicity across the different outcome measures, p-values will be adjusted using the Benjamini–Hochberg procedure. Significant results will be subjected to Bonferroni-corrected post hoc *t*-tests, and Cohen’s *d* effect sizes will be calculated.

Additionally, subgroup analyses will be conducted within the older adult group, distinguishing between different levels of cognitive impairment and frailty status. The degree of cognitive impairment and frailty status will be determined based on the initial neuropsychological assessment. Correlational analyses between cognitive variables and physical test results will also be carried out.

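### TUG and FRT have no reading between the two image conditions, so the planned TIMEPOINT (baseline, experimental) test on these two primary outcomes measures whole-session change, not the effect of the stressor

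*Protocol article*

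**What the plan says.** **Timing of TUG and FRT.**
- The Abstract says they are "administered before the low-arousal condition and after the high-arousal condition".
- Baseline physical assessment: "All these tests are performed at the beginning of the study. In addition, the TUG and FRT are repeated after the intervention".
- Procedure puts that baseline block straight after consent and before the t1 test: "Following this, baseline cognitive and physical assessments are carried out". It places the repeat after the t2 motor task: "Afterwards, the TUG and FRT are repeated".
- Outcome measurements lists them among the primary outcomes: "Balance, additionally assessed using the TUG and FRT before and after the experimental session".

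**Meaning of the labels.** The Intervention section ties baseline (t1) to the non-stressful images and experimental (t2) to the stressful ones, for example "For the experimental session (t_2_), 40 high-arousal IAPS images were selected". Outcome measurements has EMG, ground pressure and bottle IMU data recorded at both t1 and t2.

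**Analysis.** The Statistical analysis section names TUG and FRT among the primary variables. It applies one mixed factorial ANOVA model to every outcome, with GROUP and "the within-subjects factor TIMEPOINT (baseline, experimental"). The sample size in Participants is for the interaction of group with "the stimulus factor (non-stressful vs. stressful").

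**The concern.** One factor label covers two different comparisons. For the sensor outcomes, baseline against experimental compares low-arousal with high-arousal images. For TUG and FRT the first value is taken before any image and the second after everything, so the low-arousal condition is not one side of the contrast but part of what happens between the readings.

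Anything else that happens between the readings enters the TUG/FRT change in full: sitting and watching images of any kind, two runs of the motor task, and practice or fatigue over a long visit. Under the planned label that change would be read as an effect of the emotional stressor. TUG and FRT are the only clinical balance tests repeated after exposure, so a reader would give weight to such a result.

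**Working it through.** **1. Which readings exist** (Abstract, Baseline physical assessment, Outcome measurements, Procedure)

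| Outcome | Before any images | Low-arousal (t1) | High-arousal (t2) | After t2 |
|---|---|---|---|---|
| EMG, mat, IMU | no | yes | yes | no |
| TUG, FRT | yes | no | no | yes |

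The sensor outcomes fill both levels of TIMEPOINT as the protocol defines them. TUG and FRT fill neither.

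**2. The plan's own sample size.** Stated inputs are f = 0.25, alpha 0.05, power 0.80, two groups and two measurements, giving 27 per group. For the within-between interaction, lambda = N x 2 x f^2 / (1 - rho) with 1 and N - 2 df. The article gives no rho. With rho = 0.2, lambda = 54 x 2 x 0.0625 / 0.8 = 8.44 and power is 0.81, so N = 54 is reproduced (rho = 0 gives 66 and rho = 0.5 gives 34). 27 / (1 - 0.10) = 30 per group. N is not in dispute; 54 evaluable participants are used below.

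**3. Change common to both age groups, no stress effect.** Let d be the non-specific pre-to-post change in SD of the change score. Its size is not in the documents; 0.2 to 0.5 is an assumption. All figures are two-sided at 5%, before Benjamini-Hochberg adjustment.

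TIMEPOINT main effect: noncentral F(1, 52), lambda = 54 x d^2.

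| d | lambda | P(significant) |
|---|---|---|
| 0.2 | 2.16 | 0.30 |
| 0.3 | 4.86 | 0.58 |
| 0.5 | 13.5 | 0.95 |

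The same bias reaches the comparison within one age group. For a paired t-test with n = 27, the noncentrality is d x sqrt(27) = 1.04, 1.56 and 2.60, giving 0.17, 0.32 and 0.71 (without the Bonferroni correction planned for post hoc tests).

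**4. GROUP x TIMEPOINT interaction.** A change common to both groups cancels and the rejection rate stays at 5%. If the non-specific change differs between young and older adults by d SD (again assumed): noncentral F(1, 52), lambda = 27 x d^2 / 2.

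| d | lambda | P(significant) |
|---|---|---|
| 0.2 | 0.54 | 0.11 |
| 0.3 | 1.215 | 0.19 |
| 0.5 | 3.375 | 0.44 |

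**The case against.** **The before-after design is intended and disclosed.** The specific objectives present the TUG/FRT repeat as a post-intervention measure of functional balance change, and the intervention covers both image sets. This stands as a defence of the measurement schedule. It does not defend analysing that change under labels that mean t1 and t2.

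**The interaction is what the study is sized for, and common change cancels there.** This stands, and it limits the point. A reader might take the 30% to 95% as the risk to the sized test; it is not. It applies to the TIMEPOINT main effect. The interaction is affected only if non-specific change differs by age. That is plausible, since the protocol itself provides for fatigue in older adults during the cognitive battery, but no size is documented.

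**The sensor outcomes are not clean either.** Also true. With the fixed low-then-high order, having already done the motor task is in their t1-t2 contrast too. They do, however, have a low-arousal comparator, which TUG and FRT would lack whatever the order of conditions.

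**Does the protocol contradict itself on timing?** A reader might infer this from "Balance, additionally assessed using the TUG and FRT before and after the experimental session", since the Intervention section uses experimental session for t2, which would place the first reading between t1 and t2. The documents do not support that reading. The same Outcome measurements section uses the phrase when placing the maximum voluntary contractions, which serve to normalise EMG from both t1 and t2. There it most naturally means the whole image-and-task session, in line with the Abstract and Procedure. The wording is loose, not contradictory.

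**Conclusion.** The point holds as a mismatch between measurement schedule and analysis. TUG and FRT are read before any images and again only after the high-arousal test, yet they are analysed as if they had a value in each image condition. Their TIMEPOINT contrast is whole-session change and cannot be attributed to the high-arousal images.

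The main effect and the within-group comparisons are fully exposed to non-specific change. The interaction is exposed only to an age difference in that change. The rejection rates in the working rest on assumed changes of 0.2 to 0.5 SD, no stress effect, 54 evaluable participants and no multiplicity adjustment. They illustrate sensitivity and are not estimates for this study. The mismatch itself needs none of these assumptions. Neither the sample size nor the analysis of the sensor outcomes is called into question here.

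**What to change.** In Statistical analysis:
- Take TUG and FRT out of the baseline (t1) versus experimental (t2) stimulus analysis.
- Analyse and report them as pre-to-post change over the whole session, by age group. This agrees with the specific objectives and with Baseline physical assessment.
- State that this change is not attributed to the high-arousal images alone.
- Rest the stressor conclusion on the primary outcomes recorded in both conditions: EMG, ground pressure and IMU.

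In Outcome measurements, say which session is meant by experimental session in the TUG/FRT item, as a minor clarification.

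The cost is wording only, with no new data and no change to N. The downside is that TUG and FRT no longer support a stressor-specific claim.

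An extra TUG/FRT between t1 and t2 for participants still to be enrolled is optional. It would change procedures during recruitment, cover only part of the sample, and still be subject to fixed order and repeated practice, so it does not replace the relabelling.

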## Introduction

The number of people over 60 years of age, as well as the proportion they represent within the general population, is increasing [1]. In 2024, people over 60 made up 28.3% of the population in the European Union [2]. According to estimates by the World Health Organization (WHO), this trend will continue to rise over the coming decades, especially in developing countries [1].

Ageing, on a biological level, is associated with the accumulation of molecular and cellular damage that, over time, reduces the overall capacity of the individual [3,4]. Frailty, in turn, refers to the progressive deterioration of physiological systems related to age, causing a decline in capabilities, greater vulnerability to both internal and external stressors and an increased risk of adverse effects such as falls [3,5].

The WHO states that each year approximately 28% to 35% of people over 65 years old suffer a fall [6], and age is one of the main risk factors for falls [7]. Rodríguez-Molinero et al. [8] studied a sample of 772 Spanish individuals over 64 years old for a year to obtain data on the frequency of falls in the elderly population and the associated risk factors. The study results showed incidence rates similar to those reported by the WHO, with approximately one in three people experiencing a fall over the year and one in ten falling repeatedly. Muscle weakness and impaired balance were among the factors associated with the risk of falls [8].

A recent review by Wang et al. [9] on age-related changes in balance highlights the physiological changes that occur during ageing. On the one hand, age is related to changes in the visual, vestibular and proprioceptive sensory systems, which play a crucial role in spatial orientation. Specifically, the visual system provides information about the position and movement of the body relative to the environment. The vestibular system provides information about the position of the head, which is essential for coordinating body movement and stabilising vision. The proprioceptive system enables constant perception of body position in space, helping to control movement without relying on visual information. With ageing, visual information and acuity are affected, vestibular function deteriorates, and proprioceptive abilities decrease. Additionally, ageing causes a gradual decline in cognitive functions such as memory and attention, which also play an important role in postural control and balance. On the other hand, ageing is related to changes in the musculoskeletal system, such as muscle weakness and loss of bone mass. All these ageing-related changes predispose individuals to falls due to their impact on postural control and balance [9].

Given that frailty implies greater vulnerability to stress factors, several studies have also linked exposure to emotional stress with an increased risk of falls. Fink et al. [10] studied the association between emotional stress and falls in a prospective cohort of men over 65 years old. The results showed that a history of one or more stressful life events in the previous year increased the risk of falls during the following year [10]. However, Fink et al. [10] did not analyse the time interval between the occurrence of stressful life events and the falls, nor did they collect measures of perceived or physiological stress during those life events. Meanwhile, Möller et al. [11] analysed whether sudden emotional stress could trigger falls. They conducted a study with patients over 65 years old diagnosed with hip or pelvic fractures using structured interviews. They asked whether participants had experienced emotions representing emotional stress (anger, sadness, worry, anxiety or stress) on the day of injury or the day before. If the answer was yes, the exact timing of the feeling within the prior 48 hours and its frequency in the past six months were recorded, estimating annual exposure. The results showed an increased risk of falling and subsequent hip or pelvic fracture up to one hour after an episode of emotional stress [11].

However, the mechanism connecting stressful events with falls remains uncertain [10]. It has been hypothesised that the predisposition to falls following emotional stress could be explained by impaired postural control, balance and vision [11]. It has been suggested that in stressful situations, older adults may perform premature gaze shifts that could impair balance control [11]. Akinlosotu et al. [12] researched the influence of mental stress on balance perturbation responses in 23 older adults. Stress was induced through a challenging mental arithmetic task. Perturbations were applied on an instrumented treadmill designed to challenge balance within a safe environment. The results showed that mental stress immediately prior to balance perturbation reduced the effectiveness of grip responses on the handrail to maintain balance. Thus, the authors emphasised the importance of considering mental stress as a possible risk factor for falls and called for further studies with larger samples [12]. More recently, Retamal-Matus et al. [13] explored the relationship between perceived stress, physical performance and balance in 40 people over 60 years old. Perceived stress over the previous month was assessed using the Perceived Stress Scale, physical performance with the Short Physical Performance Battery (SPPB) and balance through a force platform where participants stood for 10 seconds under normal or disturbed conditions with eyes open or closed. No significant correlations were found between perceived stress and physical performance or postural control, respectively. However, as the authors note, the small sample size may have influenced the results, and the relationship between postural balance and stress is complex, requiring further research to better understand the underlying mechanisms [13]. Therefore, further research is needed to study the interactions between cognition, stress and postural control in the context of postural instability and risk of falls in older adults.

Additionally, identifying the risk factors that lead to a fall is crucial to predicting and preventing them. Traditionally, subjective and semi-subjective methods such as questionnaires and functional performance scales have been used to identify fall risk [14]. However, in recent years, different evaluation methods based on advanced technologies have been proposed to assess fall risk more objectively and reliably [14,15]. A recent systematic review by González-Castro et al. [16] aimed to analyse the evidence on the application of Artificial Intelligence (AI) in data analysis related to postural control and risk of fall. The results indicate that wearable devices (accelerometers) and deep learning AI techniques are the most widely used methods for this purpose. They also show that AI applications analysing postural control and fall risk data could be a valuable tool for creating predictive models of fall risk. Therefore, further research is needed on how technology could assist in fall prevention through early risk detection.

For all these reasons, the present project was born, titled ‘Use of Devices for Detecting Balance in Older Adults under Stress Influence (“DEPIE” from the Spanish acronym)’. Its aim is to detect whether exposure to stressful situations causes neuromuscular changes that affect postural and motor control in older adults. Studying these questions through different technological systems also allows exploration of whether technology can help prevention by detecting increased risk of falls.

Specifically, emotional stressors are expected to induce detectable neuromuscular changes via the proposed sensors. It is expected that high-arousal IAPS images will generate autonomic nervous system activation, increasing heart rate variability, possibly respiratory rate, and feelings of unease (measured with a VAS scale from 0 to 10). This may cause alterations in muscle activation, such as increased electrical activity in key muscles (tibialis anterior, gluteus medius, biceps femoris, vastus lateralis, etc.) detected by electromyography; greater sway in ground pressure (Fitness MAT) and displacements with some instability during tasks like standing up, sitting down, walking, or pouring water. In older adults, these effects could exacerbate fall risk, as observed in prior studies with acute perturbations [11,12].

Specifically, the general objectives of the DEPIE project are:

